### Recruitment {15}

Individuals are referred by the public health centres based on apparent trauma symptoms (pre-selection of eligible patients).

## Assignment of interventions: allocation

### Sequence generation {16a}

Eligible participants will be randomised to NET or TAU controlling for PTSD symptom severity and gender using a stratified block design for the initial group of 51 participants. For this, we will use the sample function in base R [31] setting a specific seed to allow for the results to be replicated. Participants who join the study later on will be randomised using a naïve minimization technique in Minimizer v.1.0.1 [32] which allows for a continuous randomisation of incrementing sample size. Minimization is based on techniques that allow to control for imbalance among patient factors and outcomes, balancing sample sizes per treatment groups [33].

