### Sample size {14}

Following similar studies in regions with ongoing violence, sample size per group was calculated based on a medium to high within-group Cohen’s *d* effect size for our primary outcome measure PTSD [18, 19, 30] with a power of >.70 and a significance level of .05, a sample size of 25 per group was suggested. However, to allow for a more robust analysis testing for a smaller effect due to the ongoing violence and in regard to covariates (level of ongoing violence) and secondary measures (depression, dissociation, substance involvement and medication, functioning), we will aim at a sample size of 30 per group.

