### Concealment mechanism {16b}

Unpredictability of assignment will be ensured by implementing randomisation of participants after the baseline interview and by one of the authors who is not involved in the clinical work (SC, based in Konstanz, Germany).

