### Implementation {16c}

Participants will be enrolled by the study coordinator (FS) and relevant information (participant code, sex and PTSD symptom severity) will be forwarded for randomisation (SC). Randomisation will consider sex (male or female) and PTSD symptom severity categories based on the PSS-I sum scores (low 7–25; low-medium 26–40; medium-high 41–55; and high 56–80).

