## Oversight and monitoring

### Composition of the coordinating centre and trial steering committee {5d}

Fiocruz is responsible for the coordination of activities on site (e.g. arrangements with the health centres, ensure availability of rooms, etc.) and ensure study implementation follows the study protocol. Interviewer and NET trainings are led by AK and FS and supervision is conducted by FS, JN and AK. Fiocruz with the support of the University of Konstanz is responsible for data management, which encompasses all tasks concerning processing and utilisation of study data, with the aim of guaranteeing high-quality data and providing a valid study database for statistical analyses. The University of Konstanz (SC) will be responsible for conducting statistical analysis and the publishing of data.

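### For patients after the 51st, off-site allocation after baseline does not by itself make the next arm unpredictable, because they are minimised on two factors and the enroller probably knows many earlier allocations

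*Protocol article*

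**What the plan says.** - **Method.** Sequence generation {16a} describes two phases: first "using a stratified block design for the initial group of 51 participants", then "Participants who join the study later on will be randomised using a naïve minimization technique". It names the software and calls the minimisation naïve. It gives no assignment probability.
- **Factors.** Implementation {16c}: "Randomisation will consider sex (male or female) and PTSD symptom severity categories based on the PSS-I sum scores". There are four bands, and their cut-offs are printed.
- **Who enrols and what is sent.** Also {16c}: "Participants will be enrolled by the study coordinator", and "relevant information (participant code, sex and PTSD symptom severity) will be forwarded for randomisation". The sender is not named, but the sentence is about the coordinator's enrolment step.
- **Claimed protection.** Concealment mechanism {16b}: "Unpredictability of assignment will be ensured by implementing randomisation of participants after the baseline interview". The second safeguard is that an author in Germany with no part in the clinical work performs the randomisation.
- **Overlap of roles.** Section {5d} has a sentence beginning "Interviewer and NET trainings are led by". It lists two people for training and three for supervision. The coordinator's initials from {16c} are in both lists.
- **Size.** Sample size {14}: "we will aim at a sample size of 30 per group".

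**The concern.** Minimisation places the next patient in the arm that evens out the running factor totals. Apart from ties and any random element, the result follows from the new patient's factor levels and the earlier allocations. Having the calculation done elsewhere does not hide it from someone on site who holds both.

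The plan puts the enrolment step with a person likely to hold both. Sex and severity are forwarded at enrolment. Someone who helps supervise NET would normally learn which patients receive it, and enrolled patients not in NET are in TAU. Strategies to improve adherence {11c} describes supervision of 2 h per week alongside the session narrations, so the contact is regular.

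An enroller who can foresee the arm may, without intending to, influence whether or when a patient is put forward. That would be selection bias in a small trial in which patients know their treatment.

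**Working it through.** The plan gives no figure for predictability, so there is none to reproduce. Its sample size calculation does not bear on this point.

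**1. Patients exposed.** The target is 2 × 30 = 60 ({14}), and blocks cover the first 51 ({16a}). That leaves 60 − 51 = 9 by minimisation, and 9/60 = 15%. The number rises if more than 60 are enrolled.

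**2. Allocation rule.** For a new patient with sex *s* and band *v*, the imbalance if placed in arm *a* is

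I(*a*) = Σ over k in {*s*, *v*} of |n(k, *a*) + 1 − n(k, other arm)|.

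The arm with the smaller I is given with probability *p*, and ties are broken at random. With no random element, *p* = 1. A variant adds the same term for the overall arm totals.

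**3. Guess rate.** An observer who knows *s*, *v* and all earlier allocations guesses the favoured arm. If τ is the share of ties, the guess rate is τ/2 + (1 − τ)*p*.

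**4. Simulation.** There were 4,000 simulated trials per setting: 51 patients in blocks within the 8 sex-by-band strata, then 9 by minimisation with totals carried over. The article does not give these inputs, so they are assumed: block size 2 or 4; 50% or 80% in one sex; bands equally likely or split 10/30/40/20%.

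| *p* | Ties, factors only | Guessed, factors only | Ties, plus arm totals | Guessed, plus arm totals |
|---|---|---|---|---|
| 1.0 | 27–28% | 86–87% | 19–20% | 90–91% |
| 0.9 | 27% | 79% | 18–19% | 83% |
| 0.8 | 26% | 72% | 16–17% | 75–76% |
| 0.7 | 25–26% | 65% | 14–15% | 67% |

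Check by the formula:
- *p* = 1, τ = 0.276: 0.138 + 0.724 = 0.862.
- *p* = 0.8, τ = 0.163: 0.0815 + 0.837 × 0.8 = 0.751.

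Block size, factor mix and 20 rather than 9 later patients change the rates by about one percentage point.

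**5. In patients.** Chance gives 9 × 0.5 = 4.5 correct guesses. With no random element the figure is 9 × 0.86 = 7.7 to 9 × 0.91 = 8.2. With *p* of 0.7–0.8 it is 9 × 0.65 = 5.9 to 9 × 0.76 = 6.8.

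**6. If totals restart after the 51st patient.** With *p* = 1 and factors only, about 80% are guessed. The mean final arm-size difference rises from about 0.6–0.9 to 1.7–2.2 patients.

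**The case against.** **Two stronger readings go beyond the text.**
- A reader might infer that the coordinator knows all past allocations. No section says so. It is an inference from initials shared between {16c} and {5d}, and three people share supervision. Only a likelihood is supported.
- A reader might infer that the next arm is in effect fixed. That needs a minimisation with no random element. The word naïve and the absence of a probability point that way but do not settle it. A condensed article may leave that setting, and whether totals continue, to the full protocol. The silence is therefore not a fault in itself. What is open to criticism is that {16b} gives reasons for unpredictability that do not suffice under the method chosen.

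**The route to bias is narrow.** Health centres refer patients ({15}). A focal point schedules the baseline visit, and trained interviewers determine eligibility ({13}). Interviewers are blinded ({17a}) and give the detailed consent information ({26a}). The severity band does not exist until that interview, so beforehand the coordinator lacks one of the two inputs. This stands, and it keeps the point small. It would also be wrong to argue from {18a} that severity scoring is exposed. The close supervision there covers interviewers' first interviews, its supervisor is not named, and it would mostly be over by the 51st patient.

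**The remedy is partial and late.** A random element of 0.7–0.8 still leaves 65–76% guessable. Trial status gives January 31, 2021 as the expected end of recruitment, so a change could come too late. Both remarks are fair. They are why the data route matters as well as the probability, and why disclosure is offered as an alternative.

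**Conclusion.** The point holds as a modest, inexpensive improvement. The two safeguards in {16b} are real concealment steps, but under two-factor minimisation they do not ensure unpredictability towards someone who holds the factors and the earlier allocations. The plan's division of roles makes the enroller a likely such person.

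The guess rates are upper figures. They describe an observer who knows every earlier allocation, whereas the coordinator may know only many of them. The 86–91% also assumes no random element and continuing totals. Even at a favoured-arm probability of 0.7, though, the guess beats chance, so the claim in {16b} is too strong whatever the software setting.

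These rates are not estimates of bias in the treatment effect. That bias is probably small, given about 9 exposed patients and eligibility and severity settled by blinded interviewers before randomisation.

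**What to change.** 1. In {16a}, run the minimisation with a stated random element, for example probability 0.7–0.8 for the arm that reduces imbalance, or confirm that the software setting already has one. State that totals continue from the first 51 patients.
2. In {16c}, have the blinded interviewer send participant code, sex and locked PSS-I score directly to the off-site randomiser, with eligibility logged as final before the arm is returned. This removes the enroller's room to act on a guess, which the random element alone does not.
3. In {16b}, rest the claim on these two safeguards. If allocation is already complete, report instead the setting used and who knew the allocations.

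**Cost.** A software setting, a changed message route and some wording. If recruitment is still open, a new probability is a change during the trial and should be documented as an amendment. The price in balance is small. With totals carried over, the mean final arm-size difference grows by about 0.5–0.7 of a patient at 0.8. The same simulation puts the increase at about one patient at 0.7, so a value nearer 0.8 keeps it under one.

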### Concealment mechanism {16b}

Unpredictability of assignment will be ensured by implementing randomisation of participants after the baseline interview and by one of the authors who is not involved in the clinical work (SC, based in Konstanz, Germany).

### Implementation {16c}

Participants will be enrolled by the study coordinator (FS) and relevant information (participant code, sex and PTSD symptom severity) will be forwarded for randomisation (SC). Randomisation will consider sex (male or female) and PTSD symptom severity categories based on the PSS-I sum scores (low 7–25; low-medium 26–40; medium-high 41–55; and high 56–80).

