### Trial design {8}

The present study is a two-arm parallel group, observer-blinded, randomised, actively controlled clinical superiority trial with an allocation ratio of 1:1.

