## Methods: participants, interventions and outcomes

### Study setting {9}

The trial is implemented in health centres in Rio de Janeiro (Brazil) in a joint project of the University of Konstanz and Claves/ENSP/Fiocruz. Collaborating health centres include Centro de Saúde Escola Germano Sinval Faria ENSP/Fiocruz, ENSP/Fiocruz (Manguinhos), Centro Municipal de Saúde Heitor Beltrão (Tijuca), potentially Clínica da Família Odaléa Firmo Dutra (Grajaú).

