#### Treatment as usual

TAU receives (or continues to receive) the services of our collaborating health centre (where they have also been recruited from). The treatment is not standardised and typically targets the symptoms reported by the patient (often diagnosed as hypertension, depression, panic disorder). TAU includes pharmacotherapy, empathic listening, problem solving and practical or social support [23]. It does not include deliberate trauma exposure which is a key characteristic of evidence-based trauma therapy. Treatment doses will be assessed retrospectively during follow-up assessments.

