## Statistical methods

### Statistical methods for primary and secondary outcomes {20a}

To test the efficacy of NET in comparison to TAU in regard to primary (PTSD) and secondary (depression, shutdown dissociation, substance involvement, functionality) outcomes, we plan to use separate generalised linear mixed models (GLMMs) in R (R Core Team, 2018). To investigate the influence of ongoing violence, we will enter the sum scores for community and intimate partner violence as fixed model terms. To account for non-independence of measurements, we will include individuals as random model terms. To account for repeated measures, we will control the within-group variance for the effect of time, i.e. baseline and 3- and 6-month follow-ups, according to Field et al. [41]. To estimate the significance of the fixed terms, we plan to fit the models using maximum likelihood (ML) and compare models with and without each fixed term using likelihood-ratio tests (LRTs) [42]. In cases where interaction terms are significant, we will use post hoc Tukey tests using the R package emmeans [43] to assess which contrasts differ significantly. To correct for multiple comparisons controlling for the false discovery rate, we will adjust *P* values using the R built-in function p.adjust according to Benjamini and Hochberg [44]. Additionally, effect sizes will be estimated by calculating Cohen’s *d* [45] for within- and between-group differences. Clinically significant change will be calculated using the reliable change index, following Jacobson et al. [46] for clinical outcomes (PTSD, depression).

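### Health centre determines which usual care a control patient gets, yet it is absent from both the allocation and the stated model: a modest loss of precision and a risk of chance shift

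*Protocol article*

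**What the plan says.** All places are in the protocol article.

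- **Trial design {8}** describes a "randomised, actively controlled clinical superiority trial with an allocation ratio of 1:1".
- **Study setting {9}** names the sites: "Collaborating health centres include Centro de Saúde Escola Germano Sinval Faria ENSP/Fiocruz" in Manguinhos, then "Centro Municipal de Saúde Heitor Beltrão (Tijuca), potentially Clínica da Família Odaléa Firmo Dutra (Grajaú"). That is two centres in different districts and a possible third.
- **Treatment as usual** ties the comparator to the recruiting site: "TAU receives (or continues to receive) the services of our collaborating health centre (where they have also been recruited from"). It adds: "The treatment is not standardised and typically targets the symptoms reported by the patient".
- **Implementation {16c}** fixes the allocation factors: "Randomisation will consider sex (male or female) and PTSD symptom severity categories based on the PSS-I sum scores". There are four severity bands. It also lists what reaches the randomiser: "relevant information (participant code, sex and PTSD symptom severity) will be forwarded for randomisation".
- **Sequence generation {16a}** uses stratified blocks for the first 51 patients and minimisation afterwards.
- **Statistical methods {20a}** enters community and intimate partner violence scores as fixed terms, models baseline and the 3- and 6-month follow-ups, and states: "To account for non-independence of measurements, we will include individuals as random model terms". No centre term is listed, and section 20b does not name centre among its possible subgroups.

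**The concern.** Centre decides where a control patient is treated and can shape what that patient receives. It may also go with the level of violence around the patient. A factor that can affect the outcome through both routes is normally balanced at allocation, adjusted for in the model, or both. Here it is neither. As section 16c is written, even the minimisation cannot balance it, because the randomiser is not told the centre.

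With about 30 patients per arm, one centre can by chance supply clearly more NET than TAU patients. If patients at the centres change at different rates, part of that difference then appears in the NET-TAU contrast, in either direction. The trial has little precision to spare: section 14 plans for power just above 0.70.

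**Working it through.** **The plan's own figures.** The plan gives no figure on centre. Its only related number is 25 per group for power above 0.70 at a significance level of .05, raised to 30. The effect size has no numerical value, so 25 cannot be strictly reproduced. A within-group d of 0.5, two-sided, gives ((1.960 + 0.524)/0.5)² = 24.7, hence 25. As a between-group comparison, 25 per arm needs d of about 0.70 (power 0.697). The power figures below therefore assume d = 0.7 with 30 per arm.

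**Inputs.** From the document: 1:1 allocation, target 60, allocation factors sex (2) by severity (4), first 51 by block. Assumed, because the document does not say: patients per centre, and the size of any difference between centres.

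**1. How often centre is imbalanced.** Let a centre supply m of 60 patients and let X be the number allocated to NET. If allocation ignores centre, X is hypergeometric (60, m, 30). The NET-minus-TAU difference in that centre's share of an arm is (2X − m)/30. For m = 30, Var(X) = 30 × 0.5 × 0.5 × 30/59 = 3.81, so the SD of the difference in share is 2 × 1.95/30 = 0.13.

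| Centre size m | Split giving at least 20 points | Probability |
|---|---|---|
| 30 | 18:12 or worse | 0.196 |
| 20 | 13:7 or worse | 0.170 |
| 15 | 11:4 or worse | 0.072 |

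For m = 30, a split of 19:11 or worse has probability 0.070. These figures treat allocation as simple 30:30. Stratifying on sex and severity would lower them only as far as those factors go with centre.

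**2. What an 18:12 split does.** The centre makes up 18/30 = 60% of NET and 12/30 = 40% of TAU. Assume the centres differ by 8 PSS-I points in change.
- Both arms affected: (0.60 − 0.40) × 8 = 1.6 points (1 to 2 points for a difference of 5 to 10).
- TAU only affected: the centre's share of TAU moves from 50% to 40%, so (0.50 − 0.40) × 8 = 0.8 points (0.5 to 1 for 5 to 10).

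In SD units, with both arms affected, a 20-point imbalance shifts the contrast by 0.04, 0.10 or 0.16 SD for centre differences of 0.2, 0.5 or 0.8 SD.

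**3. Effect over repeated trials.** Simulation with 8,000 runs per setting, one endpoint, a linear model, simple 30:30 allocation, within-centre SD 1, d = 0.7, and centres of 30/30 or 40/20:

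| Centre difference | Power, no centre term | Power, centre term |
|---|---|---|
| 0 | 0.76–0.77 | 0.75–0.76 |
| 0.5 SD | 0.73–0.74 | 0.75–0.76 |
| 0.8 SD | 0.70 | 0.75 |

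Without the term, the mean estimate is 0.70 for a true 0.70 and type I error is about 0.05. The SD of the estimate rises from 0.26 to about 0.27 at 0.5 SD and 0.27–0.28 at 0.8 SD. Read with change from baseline as the endpoint, these are the figures for a centre term on change.

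**4. How far late minimisation helps.** Against the target, 60 − 51 = 9 patients fall under minimisation. In simplified simulations (two equal centres, minimising on centre and arm totals only, totals seeded from the first 51), an 18:12 or worse split fell from about 20% to about 1% in one run. It fell to about 3% in a second run that always took the better arm with equal weights. With the better arm taken only 80% of the time, the figure was about 9%. The gain is real, but its size depends on the settings of the minimisation.

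**The case against.** The strongest case against has five parts.

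- **Ordinary sampling error.** Chance imbalance in an unstratified factor does not bias the estimate or inflate type I error, and the simulation agrees. This stands, and it limits the point to precision and chance shift.
- **Violence is already in the model.** Section 20a enters each patient's violence scores, which is more direct than a centre label. This stands for the exposure route. It does not cover differences in the content of TAU.
- **Baseline is modelled.** With baseline as a time point and a random term per individual, stable differences in level between centres largely cancel. This stands. Differences in change remain, and differing local TAU would produce exactly those. It also means that a centre main effect alone would barely move the treatment-by-time contrast.
- **Few patients remain.** About nine fall under minimisation, and section Trial status expects recruitment to end on January 31, 2021, fifteen days after the last listed revision. This limits the allocation remedy but does not defeat it, as step 4 shows. The model terms apply to every patient.
- **A separate analysis plan could add centre.** It could, for the model. The allocation factors, however, are stated outright in section 16c, and an analysis plan cannot balance patients already allocated.

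A reader might also infer that a third centre joining late is the most exposed because it is small. The arithmetic says otherwise: a 20-point imbalance becomes less likely as the centre shrinks (20% at 30 patients, 7% at 15). The document says only that this centre is a possible addition, not that it opens late.

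**Conclusion.** The point holds as a moderate one that should be acted on because acting is cheap. Centre can influence the comparator and is left out of both the stated allocation factors and the stated model. The cost is a modest loss of precision. Power falls from about 0.76–0.77 to 0.73–0.74 at an assumed 0.5 SD centre difference and to 0.70 at 0.8 SD. There is also about a one-in-five chance of an 18:12 or worse split if a centre supplies half the patients.

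It is tempting to read this as a biased comparison or a false-positive risk. Nothing in the document or the calculations supports that. Nor does the document say that TAU differs systematically between centres; it says that TAU is not standardised. If such a difference exists, it acts in one arm only. The matching shift is then about 0.8 points rather than 1.6, and the treatment effect itself varies by centre, which balancing centre does not remove.

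Everything quantitative rests on assumed centre sizes, assumed centre differences in change, and d = 0.7.

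**What to change.** **Implementation {16c}.** Forward the health centre together with code, sex and severity. Add it as a minimisation factor for all patients still to be allocated, with totals seeded from those already allocated. Do not add it to the blocked strata: 8 cells by 2 or 3 centres gives 16 to 24 cells for 51 patients, or about two to three patients per cell. If recruitment has closed, only the next change applies.

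**Statistical methods {20a}.** Pre-specify centre and centre-by-time as fixed terms in the primary PSS-I model. The interaction with time is needed because the contrast of interest is a difference in change. Fix a rule for merging very small centres before unblinded data are seen. Showing NET-TAU results by centre descriptively would let readers judge whether the effect varies with the local TAU.

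**Cost.** One more field to forward, slightly looser balance on sex and severity, and a few degrees of freedom. So the added factor is cheap but not free. If the centres do not differ in change, the model terms cost about one percentage point of power or less. Stating them now also avoids the appearance of selection if centre were added after results are known.

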### Intervention description {11a}

#### NET counsellors

Trained Brazilian health personnel (medical/family doctors, psychologists) and advanced psychology students will deliver NET under constant supervision by a NET expert.

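### The named model terms omit the randomisation factors and use baseline only as a repeated outcome; conditioning on baseline would be more precise, and clustering by NET therapist needs a sensitivity analysis

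*Protocol article*

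**What the plan says.** **Allocation.** Sequence generation {16a} randomises "controlling for PTSD symptom severity and gender using a stratified block design for the initial group of 51 participants". For the rest, "Participants who join the study later on will be randomised using a naïve minimization technique". Implementation {16c} names the factors: "Randomisation will consider sex (male or female) and PTSD symptom severity categories based on the PSS-I sum scores", with four score bands.

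**Model.** The statistical methods section {20a} says "we plan to use separate generalised linear mixed models (GLMMs) in R", one model per outcome. For fixed terms, "we will enter the sum scores for community and intimate partner violence as fixed model terms". For dependence, "To account for non-independence of measurements, we will include individuals as random model terms". Time has three levels (baseline, 3 months, 6 months), so baseline PSS-I is in the PTSD model as its first repeated measurement. Sex and severity band are not named as adjustment terms. Sex returns only as a possible subgroup in {20b}. The treatment term is not written out; the section refers only to interaction terms being followed by post hoc tests.

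**Therapists.** Under NET counsellors, health personnel and advanced psychology students "will deliver NET under constant supervision by a NET expert". Sessions are individual. The number of counsellors is not given, and no therapist term is named.

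**The concern.** The factors that drive allocation would normally appear in the analysis. Here they are collected, used to balance the arms, and then not named in the model.

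With baseline as one level of time, the natural treatment test is arm-by-time. If each arm keeps its own baseline mean, that test compares changes from baseline. Randomisation makes the expected baseline means equal, so estimating them separately gives away precision. In a trial of 30 per group, planned for power just above 0.70, that matters.

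The therapist question is separate and runs the other way. If several NET patients share a therapist and their outcomes are correlated, a random term for individuals alone gives standard errors that are too small.

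**Working it through.** **1. The plan's own figure.** The Sample size section gives 25 per group, power above 0.70, alpha 0.05 and a medium to high within-group d without a number. It can only be back-solved. Two-sided t tests with 25 per group reach power 0.70 at d of about 0.72 (two-sample) or 0.52 (paired). Both fit the description, so 25 is neither confirmed nor refuted. The target of 30 per group is used below.

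**2. Change contrast against conditioning on baseline.** Inputs: 30 per group (protocol); correlation r between baseline and follow-up, and between-group d in units of the single-visit SD (both assumed); a single follow-up.

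- Variance of the change contrast is proportional to 2(1−r).
- Variance after conditioning on baseline is proportional to 1−r².
- Ratio: (1−r²)/[2(1−r)] = (1+r)/2.

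| r | Ratio | Equivalent gain in patients |
|---|---|---|
| 0.4 | 0.70 | 1/0.70 − 1 = 43% |
| 0.5 | 0.75 | 1/0.75 − 1 = 33% |
| 0.6 | 0.80 | 1/0.80 − 1 = 25% |

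Power by t test at r = 0.5: 0.697 to 0.816 at d = 0.65, and 0.478 to 0.594 at d = 0.5. By normal approximation at d = 0.65: 0.567 to 0.751 (r = 0.3), 0.711 to 0.828 (r = 0.5), 0.901 to 0.941 (r = 0.7). The gain shrinks as r rises.

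**3. Adding sex and severity bands as main effects.** Random-intercept models were fitted by maximum likelihood to 40 simulated trials (30 per arm, three visits), and the arm-by-time contrast at the last visit was read off.

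- Complete data: mean standard error 0.2494 with neither factor, with sex, and with sex and severity band. The estimates did not change.
- 15% of follow-up visits missing: 0.259 without the factors, 0.256 with both.

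With complete data, a covariate whose effect is constant over time cancels out of a within-person contrast.

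**4. If the test were instead a single follow-up comparison.** Let R² be the share of outcome variance explained by the balanced factors (assumed 0.05 to 0.40), with 30 per arm and d = 0.65. Leaving the factors out gives type I error 0.044 down to 0.011 and power 0.716 to 0.764. Adjusting gives power 0.733 to 0.901. The omission is conservative.

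**5. Therapist clustering in the NET arm.** Inputs, all assumed: m = 3 to 10 patients per therapist, ICC 0.02 to 0.10. Design effect DE = 1+(m−1)ICC; true over model standard error = √[(1+DE)/2]; type I error = 2[1−Φ(1.96/ratio)].

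| m | ICC | DE | SE ratio | Type I error |
|---|---|---|---|---|
| 3 | 0.02 | 1.04 | 1.010 | 0.052 |
| 5 | 0.05 | 1.20 | 1.049 | 0.062 |
| 6 | 0.05 | 1.25 | 1.061 | 0.065 |
| 10 | 0.10 | 1.90 | 1.204 | 0.104 |

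At m = 6 and ICC 0.05, with d = 0.65, power is 0.660 once therapist is modelled, against 0.711 with no clustering.

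**The case against.** The strongest reply is that {20a} describes purposes and does not give a model formula. It does not even write out the treatment term, so its list need not be exhaustive, and a separate analysis plan could add covariates or constrain the baseline means. This stands in part. It means that the change contrast is an inference and the loss cannot be fixed from the article. It does not remove the point, because the section does choose which covariates enter and which dependence is modelled, and those choices do not reflect the allocation scheme.

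A reader might also infer three stronger things that the documents do not support:

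- *That severity is missing from the primary model.* Baseline PSS-I, from which the bands are formed, is there as a repeated outcome. It is absent only from the models for the secondary outcomes.
- *That naming sex and severity band in the model would recover the power.* Step 3 shows that it would not for an arm-by-time test.
- *That omitting the therapist also costs power.* It makes standard errors too small, and modelling it lowers power.

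It is also fair to say that nothing states how many patients each counsellor treats. Ten per therapist among 30 NET patients would mean about three therapists, too few to estimate a therapist variance well. The therapist term therefore belongs in a sensitivity analysis.

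**Conclusion.** The point holds in a limited form. The model terms named in {20a} include neither randomisation factor as an adjustment term, and baseline is used only as a repeated outcome. If treatment is tested as arm-by-time with free baseline means, conditioning on baseline would cut the variance to 0.70 to 0.80 of its value for r between 0.4 and 0.6. At r = 0.5 and d = 0.65 that is about 12 points of power at 30 per group. The test term, r and the between-group d are not in the documents, so these sizes are conditional. They do not establish what the trial's power is.

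Possible clustering by NET therapist is a secondary point in the opposite direction. Type I error would be about 5% to 10% over the assumed range, which rests on an unstated number of therapists and ICC.

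**What to change.** In {20a}, write out the treatment contrast and make these changes:

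- **Primary outcome.** Use a longitudinal model with the arm means constrained equal at baseline. This keeps participants who have baseline data only, in line with {20c}, which analyses everyone with reliable baseline data as randomised. The alternative is continuous baseline PSS-I-5 as a covariate with T1 and T2 as outcomes; that version drops participants with no follow-up unless their values are imputed.
- **Sex.** Include it as a fixed term.
- **Secondary outcomes.** Treat each in the same way with its own baseline, and add baseline PSS-I-5 because severity was a randomisation factor.
- **Therapist.** Record therapist identity with the data and prespecify a sensitivity analysis with a therapist random effect in the NET arm only.

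The cost is wording, plus keeping the therapist code; sex and PSS-I are already recorded for randomisation. The therapist analysis will lower power, and its variance will be poorly estimated if therapists are few. No interim analysis is planned, so the change can be settled before any comparison of the arms is seen.
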